### Unblinding

2.5

Staff members who perform the ES and the biostatistician who performs the allocation are not blind. Data will be unblinded when data analysis is completed and statistical tests between study groups need to be performed.

### Inclusion/exclusion criteria

2.6

The inclusion criteria for the participants are the following:

Meet the criteria for ischemic stroke in the Chinese Guidelines for the Diagnosis and Treatment of Acute Ischemic Stroke 2023, and confirmed by CT or MRI of the head.The patient had a first-time stroke with unilateral hemiplegia.Onset ranged from 2 weeks to 3 months, and vital signs were stable.Age 45–80 years old.The patient had upper limb motor dysfunction in clinical manifestations, and FMA-UE scores in the 0–30 range.The patient can sit independently for 1 h or more.Patients who are in stable condition, conscious, have no aphasia or disorder, can understand the content of the scale, and cooperate with examination and treatment.The patient has not taken any sedative medication or muscle relaxant for 2 weeks.Informed consent to this trial, and signed written informed consent.

The exclusion criteria for the participants are the following:

Patients who are critically ill or in the acute phase and whose condition has not yet stabilized.Patients with deafness, aphasia, or severe cognitive impairment that make it difficult to communicate normally.Patients with systolic blood pressure > 180 mmHg or diastolic blood pressure > 110 mmHg, patients with severe cardiovascular, liver, kidney, blood, digestive, respiratory and other primary diseases, patients with mental illness, malignant tumors, venous thrombosis, osteoporosis, severe bleeding tendency and infection at the treatment site.Patients who are unable to recover with the study protocol or participate in other clinical experiments within 3 months or receive other related treatments in the middle of the study, which may affect the efficacy judgment of this study.Dystonia and previous motor dysfunction caused by other reasons.Pregnant and lactating women.Hemiplegia upper limb with previous trauma and bone and joint diseases.The patient is in a state of severe spasticity, i.e., modified Ashworth scale above grade IIII.The patient has pacemakers, cochlear implants and other instruments and equipment in the body.The patient has had vagus nerve surgery.The patient has sensory disturbances of the skin.

Data integrity is compromised and data will not be included in the analyses when the following:

The patient voluntarily requested to withdraw.The patient is concurrently involved in other similar therapeutic activities.The patient compliance with the experiment was poor.The patient develops other conditions or serious adverse events that affect the experiment.

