#### Relevant concomitant care permitted or prohibited during the trial

2.12.6

During the trial period, registered participants are prohibited from enrolling in other clinical trials. The research team will provide periodic reminders to participants to refrain from initiating any additional rehabilitation programs throughout the study duration. This approach is essential to maintain the validity and reliability of the research findings.

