#### Methods in analysis to handle protocol non-adherence and any statistical methods to handle missing data

2.15.2

If patients have adverse reactions and discomfort during the trial, the trial will be stopped immediately and relevant information will be recorded. If the patient has been involved in the evaluation and treatment for more than 2 weeks, the data of the patient should still be recorded and counted. If the patient offers to suspend the trial, he should immediately stop the trial and record the reason for the suspension in time. We will conduct an Intention-to-Treat analysis, incorporating all randomly assigned participants, regardless of whether they withdrew prematurely. This approach maintains the original random allocation, minimizes selection bias, and preserves the sample’s randomness.

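### The fourth exclusion criterion in section 2.6 covers events after randomisation and, with the data-removal list beside it, contradicts the intention-to-treat analysis in section 2.15.2

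*Protocol article*

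**What the plan says.** Section 2.6 (Inclusion/exclusion criteria) gives, as the fourth exclusion criterion, "Patients who are unable to recover with the study protocol or participate in other clinical experiments within 3 months or receive other related treatments", and places the last of these "in the middle of the study, which may affect the efficacy judgment of this study".

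The same section then sets a separate rule: "Data integrity is compromised and data will not be included in the analyses when the following". Four triggers follow: voluntary withdrawal; "The patient is concurrently involved in other similar therapeutic activities"; "The patient compliance with the experiment was poor"; and other conditions or serious adverse events that affect the experiment. Lack of recovery is not among them.

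Section 2.9 (Participant timeline) has patients meet the screening criteria before baseline assessment, consent and randomisation. Section 2.12.6 bars enrolment in other trials and says participants will be reminded to "refrain from initiating any additional rehabilitation programs throughout the study duration". Section 2.15.2 states: "We will conduct an Intention-to-Treat analysis, incorporating all randomly assigned participants, regardless of whether they withdrew prematurely".

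**The concern.** An eligibility criterion should be answerable before allocation. One part of this criterion, related treatment during the study, can only be met afterwards. A second part, non-recovery under the protocol, would also be post-randomisation if taken at its word. The reason given is the effect on the efficacy judgment, so the clause concerns who counts in the result and not who is suitable to enter.

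At stake is the primary comparison of FMA-UE. Patients who take up another therapy may differ in outcome from those who do not, and the frequency may differ between active and sham. Leaving them out would then break the comparability that randomisation provides. If the data-removal list alone were repaired, a patient who started related treatment after randomisation would still meet a listed exclusion criterion, and the article does not say how such a patient is handled.

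**Working it through.** **1. When each part of the criterion can be known**

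| Part of the fourth exclusion criterion | Known at screening (section 2.9)? |
|---|---|
| Unable to recover under the protocol, literal sense | No; it needs treatment and outcome |
| Same phrase, if it means unable to undergo the protocol's rehabilitation | Yes |
| Other clinical experiments within 3 months | Yes, if it means the 3 months before entry |
| Other related treatments during the study | No, on any reading |

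At least one part is therefore a post-randomisation event.

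**2. Fate of the same randomised patient under two sections**

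| Event after randomisation | Section 2.6 | Section 2.15.2 |
|---|---|---|
| Starts similar or related therapy | Meets an exclusion criterion; data also dropped by the list | Analysed |
| Withdraws voluntarily | Data dropped by the list | Analysed, stated explicitly |
| Poor compliance | Data dropped by the list; no threshold given | Analysed |
| Does not recover | Meets the criterion only if the phrase is literal; not on the list | Analysed |

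The first three rows are contradictions in the text as it stands. The fourth depends on the reading. No sentence says which section takes precedence.

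**3. The plan's own numbers**

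Section 2.2 gives 20 per group, inflated for about 20% drop-out: 20 / (1 − 0.20) = 25, which reproduces. The allowance is 25 − 20 = 5 per group, and removals under section 2.6 would draw on the same 5. One patient is 1/25 = 4% of an arm. The n of 20 itself cannot be checked, because no SD is stated. For a 5.25-point difference, two-sided alpha 0.05 and power 0.80, n = 20 implies an SD of about 5.93 (normal approximation) or 5.77 (t test).

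**4. Scale, purely hypothetical**

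Assumptions: no true effect; normal FMA-UE change with mean 3 or 5.25 in both arms; SD 5.93 or 8; 25 per arm; two-sided t test at 0.05; 20,000 simulated trials per setting.

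| Removed | Bias (points) | Type I error |
|---|---|---|
| None | about 0 | about 5% |
| 2 worst changes, active arm only | +0.9 to +1.2 | about 9–10% |
| 5 worst changes, active arm only | +2.0 to +2.7 | about 24% |
| 5 worst changes, both arms | about 0 | about 10% |

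These rows show only how sensitive a trial of this size is to removal that follows outcome. The article states no such rule, number or arm. If removals were unrelated to outcome, the cost would be lost precision and not bias.

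**The case against.** A reader might infer that non-responders can be declared ineligible once their FMA-UE result is known. The documents do not support that. The non-recovery phrase has no threshold, no time point and no mention of FMA-UE. It stands in a pre-enrolment list, where inability to undergo the rehabilitation is a natural meaning. The 5.25-point response in section 2.13.1 is not tied to eligibility. The one explicit list of reasons for dropping data does not name lack of recovery, and nothing describes re-screening randomised patients. Section 2.5 says the staff giving the stimulation are not blind, but nothing gives them outcome data or authority to exclude, and section 2.4 keeps the evaluator blind. This part of the objection stands in full.

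A second argument is that the intention-to-treat sentence settles the matter, since a patient who later meets a criterion has still been randomly assigned. That is how the conflict should be resolved, but the article does not resolve it: section 2.6 says just as plainly that certain data stay out of the analyses.

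Third, co-treatment may be rare. Patients are hospitalised, the intervention lasts two weeks, and reminders are planned. This bears on how often the conflict would arise, not on whether it exists.

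Fourth, the treatment clause largely duplicates the data-removal trigger, so one clear rule could settle both. This is partly right. But the criterion is a separate sentence, and correcting only the list would leave a post-randomisation event among the eligibility criteria.

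**Conclusion.** Wrong as written, and it should be corrected. The fourth exclusion criterion contains an event that can occur only after enrolment, plus an ambiguous phrase that is outcome-dependent if taken literally. Read with the data-removal rule in section 2.6, it lets randomised patients be left out for post-randomisation events, against section 2.15.2.

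The conclusion rests on the wording of sections 2.6, 2.9 and 2.15.2 and on no numerical assumption. The size of any bias cannot be derived from the article. The simulated figures are conditional on outcome-related removal and on an assumed SD, and they are not a forecast for this trial. The claim that non-responders would be removed after their result is known is not part of this finding.

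**What to change.** - In section 2.6, restrict the fourth exclusion criterion to facts known before randomisation: for example, unable to take part in the protocol's rehabilitation procedures at screening, or participation in another trial within the previous 3 months.
- Delete or reword the non-recovery phrase, and take the clause on related treatment during the study out of eligibility.
- In section 2.12.6, record related treatment started after randomisation, with type and date, as a protocol deviation.
- State that such patients stay in follow-up and in the primary intention-to-treat analysis, and reconcile the data-removal list in section 2.6 with section 2.15.2.

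The cost is a few sentences and an ethics submission, which section 2.19 already requires when eligibility criteria or analyses change. No visits or patients are added. Little is lost at screening, because the inclusion criteria already require patients to cooperate with examination and treatment. The small downside is that a few co-treated patients remain in the primary analysis.

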#### Criteria for discontinuing interventions

2.12.4

If the patient develops other medical conditions during the intervention that interfere with the intervention, the intervention should be discontinued immediately and the circumstances documented. If the patient has participated in the assessment and intervention for more than 2 weeks, the patient’s data should still be recorded and counted; if the patient initiates discontinuation of the intervention during the intervention, the intervention should be discontinued immediately and the reason for discontinuation should be recorded in a timely manner.

Interventions will be halted if unanticipated problems (UPs) or serious adverse events (SAEs) arise that raise concerns about the intervention’s safety. Additionally, if new information emerges during the trial that warrants discontinuation, the trial will be stopped accordingly. Currently, numerous published studies have utilized 40-Hz sensory stimulation to evoke gamma oscillations in healthy subjects and Alzheimer’s patients, and no serious adverse effects have been reported. Our group is conducting a clinical trial of 40-Hz sensory stimulation induced gamma oscillations for stroke rehabilitation, and no adverse events have occurred.

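### Section 2.6 drops withdrawn and non-compliant patients from the analyses, while Section 2.15.2 promises intention-to-treat on everyone randomised

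*Protocol article*

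**What the plan says.** **Section 2.6 (Inclusion/exclusion criteria).** After the eligibility lists comes a further list headed "Data integrity is compromised and data will not be included in the analyses when the following". It names four situations. Three are "The patient voluntarily requested to withdraw", "The patient compliance with the experiment was poor" and "The patient develops other conditions or serious adverse events that affect the experiment". The fourth is taking part in similar therapy at the same time.

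**Section 2.15.2 (non-adherence and missing data).** "We will conduct an Intention-to-Treat analysis, incorporating all randomly assigned participants, regardless of whether they withdrew prematurely". The stated reason is that "This approach maintains the original random allocation, minimizes selection bias".

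**Sections 2.12.4 and 2.15.2 (stopped patients).** Both say that if a patient has been "involved in the evaluation and treatment for more than 2 weeks, the data of the patient should still be recorded and counted" (wording of Section 2.15.2; Section 2.12.4 is nearly the same). Section 2.12.4 also says: "If the patient develops other medical conditions during the intervention that interfere with the intervention, the intervention should be discontinued immediately".

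**Timing.** Section 2.9 places randomisation with the baseline assessment, before the ten sessions. The course lasts two weeks (Section 2.1), and the final assessment takes place at the tenth session (Section 2.9).

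**The concern.** The two rules give opposite answers for the same patient. Withdrawal is the plainest case: Section 2.6 removes the patient and Section 2.15.2 expressly keeps the patient. Poor compliers, users of concurrent therapy, and patients whose illness or serious adverse event affects the experiment are also removed by one rule and kept by the other, because all of them have been randomised.

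Withdrawal, compliance and adverse events can depend on treatment. One arm receives current raised to tolerance and the other receives none (Sections 2.12.1 and 2.12.2). Removing patients for such reasons means the groups compared are no longer those that randomisation formed. Section 2.6 also sets no threshold for poor compliance and no test for what affects the experiment, so part of the exclusion is discretionary. With both rules in print, either analysis set could later be reported as the planned one.

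**Working it through.** **1. The plan's own figure.** Section 2.2 takes 20 evaluable patients per group and allows about 20% drop-out: 20 / (1 − 0.20) = 25 per group, 50 in total. This reproduces.

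**2. Patients in dispute.** At that allowance, 0.20 × 25 = 5 per arm, or 10 in total.
- Under Section 2.15.2 the analysis set is 50.
- Under Section 2.6 it could be as small as 50 − 10 = 40, if every drop-out meets one of the four listed reasons (an assumption).

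Forty is the 20 per arm that Section 2.2 plans for. The issue is therefore selection, not a loss of planned power. The figure of 50 also presumes that patients without an observed outcome enter the analysis by some stated method.

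**3. The rules side by side.**

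| Patient | Section 2.6 | Section 2.15.2, ITT sentence |
|---|---|---|
| Withdraws at own request | out | in |
| Complies poorly | out | in |
| Similar therapy alongside the trial | out | in |
| Condition or serious adverse event that affects the experiment | out | in |

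**4. Does the two-week sentence reconcile them?** No. It says data are retained after more than two weeks of participation, in a course that lasts two weeks. A patient stopped early would generally not reach that point, so the sentence does not settle that patient's status. It does not say that shorter participation leads to exclusion. Taken literally, it is unclear but compatible with intention-to-treat.

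**5. Form of any bias.** Let f be the share of an arm excluded, K the mean of those kept and E the mean of those excluded. The full-arm mean is (1 − f)K + fE, so using only the kept patients shifts it by f(K − E) = f × d. The shift in the difference between arms is f₁d₁ − f₀d₀.
- With f = 0.20 in one arm only, each FMA-UE point of d shifts the comparison by 0.20 points.
- With f = 0.20 in both arms and d equal in size but opposite in sign, each point shifts it by 0.40.
- If f × d is the same in both arms, the shift is 0.

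The protocol gives no value for d and no split of losses by arm, so neither the size nor the sign can be computed.

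**The case against.** The best defence is that Section 2.15.2 carries the heading on non-adherence and missing data and so governs, with the Section 2.6 list meant for a per-protocol set that an unseen analysis plan would label. That is possible, but the article does not say so: Section 2.6 speaks of the analyses without limit and no per-protocol set is named. This is also not a detail left to another document, since both rules are stated here. The trial is described as exploratory (Section 2.1). That tempers the severity but does not make the rules compatible.

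Four stronger readings are tempting, and the document does not support them.
- **Data count only after two weeks.** A reader might infer a third exclusion rule from the two-week sentence. The sentence includes longer participants and does not exclude shorter ones.
- **Every patient with a serious adverse event is removed.** Section 2.6 covers only events that affect the experiment.
- **Every listed reason acts after randomisation.** The list gives no timing, and other related treatment is also an eligibility matter in Section 2.6. Most of the reasons, not necessarily all, would act after randomisation.
- **The bias can be given in points.** A reader might put the 4.25 to 7.25 points of Section 2.2 in for d. Those are clinically important differences and say nothing about how kept and excluded patients differ.

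**Conclusion.** The contradiction between Section 2.6 and Section 2.15.2 is established by the text and needs no assumption. It leaves the analysis set for the primary outcome undetermined. Up to about 10 of 50 patients are affected, assuming the planned 20% drop-out occurs and every drop-out meets a Section 2.6 reason. Applying Section 2.6 would forfeit the protection that Section 2.15.2 claims. How far, and in favour of which arm, cannot be known from the protocol. The two-week sentence is a secondary lack of clarity, not a further contradiction. The point should be corrected, and the plan can be repaired without changing the design or the sample size.

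**What to change.** 1. State one rule for the primary analysis: all randomised patients, in the arm to which they were allocated.
2. Delete the Section 2.6 exclusions from that analysis, or confine them to a labelled per-protocol sensitivity set.
3. Delete or reword the two-week condition in Sections 2.12.4 and 2.15.2.
4. Seek the week-2 FMA-UE at its scheduled time from patients whose intervention stopped but who still consent to follow-up.
5. Include patients whose outcome is missing by a stated missing-data method.

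**Cost.** No additional patients. Section 2.19 requires a revised protocol to go to the ethics committee when analyses change, and recruitment began in October 2024, so this is an amendment to a running trial. Step 4 is a procedural change as well as a wording change: the week-2 assessment is tied to the tenth session, so for stopped patients it would have to be arranged without one. The amendment should be settled before the groups are unblinded for testing (Section 2.5).

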### Study setting

2.7

The study will be conducted in the Seventh People’s Hospital of Shanghai University of Traditional Chinese Medicine. All participants are given a unique identifying number that is used on all clinical trial data for that participant. The database will be constructed using Excel (Microsoft, USA 2022 version), and regular data monitoring will be undertaken in accordance with the sponsor’s standard operating procedures. Clinical data in paper format are kept in a locked file cabinet, while clinical data entered directly from the source documents along with the trial data are saved with a unique code in password-protected computers.

### Recruitment

2.8

This clinical study will be conducted at the same location with participants without blind spots for treatment task assignment. This study is aimed at patients diagnosed with stroke and associated with upper limb motor dysfunction in the Seventh People’s Hospital of Shanghai University of Traditional Chinese Medicine. Participants will be recruited by distributing pamphlets, websites, and ads on social media. To ensure effective recruitment, research team members will assist in contacting potential participants. Demographic information for each participant will be collected at the first appointment (enrollment). Participants will not be limited by age, gender, or ethnicity. Eligible participants will be informed about the study procedures and any further arrangements are required to be made. Recruitment will be stopped when the number of patients reaches the number of patients expected.

### Participant timeline

2.9

The participant timeline is shown in Figure 2. Participants who meet the screening criteria will undergo a “Baseline assessment” and complete an informed consent form and randomization. Participants in the trial group will undergo conventional rehabilitation treatment over a two-week period and complete 10 ES interventions. Control group participants will undergo conventional rehabilitation treatment over a two-week period and complete 10 sham ES interventions. Conventional rehabilitation treatment include proper limb positioning, transfer training, range of motion exercises, standing training, walking training, aerobic exercise, progressive resistance training, task-specific training, constraint-induced movement therapy, balance training, and mirror therapy (41). The 1-week post-intervention assessment will be conducted at the fifth intervention and the 2-week post-intervention assessment will be conducted at the tenth intervention.

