### Sample size

2.2

According to the previous literature, the clinically important difference of the FMA-UE scores ranged from 4.25 to 7.25 points, and the improvement of FMA-UE score of 5.25 marks a significant improvement in upper limb motor function (40). Let *α* = 0.05 (bilateral), the power at 0.80. According software, *n* = 20 can be obtained, and with a drop-out rate of around 20%, the sample size required for each group is 25 cases each. Furthermore, we will establish robust communication protocols during the study to minimize participant dropout and ensure adequate final sample size. Before the study begins, we will thoroughly explain its importance and significance to participants, fostering their comprehension and willingness to cooperate. Throughout the study, we will promptly address any questions or concerns that arise, maintaining participant engagement.

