### Outcomes

2.13

All patients will receive baseline assessment, 1-week post-intervention assessment and 2-week post-intervention assessment. The primary outcome is the FMA-UE. The secondary indicators include EEG, NIHSS, MMSE and MBI.

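### The week-1 and week-2 assessments are tied to the fifth and tenth sessions, so a patient who stops ES early has no clearly scheduled week-2 FMA-UE, although all patients are to be assessed and analysed by intention to treat

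*Protocol article*

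**What the plan says.** Section 2.9 (Participant timeline) sets both follow-up assessments by session count: the week-1 assessment falls at the fifth session, and "the 2-week post-intervention assessment will be conducted at the tenth intervention". The same section has trial-group patients "undergo conventional rehabilitation treatment over a two-week period and complete 10 ES interventions"; section 2.1 gives the rhythm as five sessions a week for two weeks. The caption of Figure 2 labels the final assessment, t4, as the 2-week assessment.

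Section 2.12.4 covers stopping. For an intercurrent medical condition, ES ends and the circumstances are documented. Where the patient chooses to stop, "the intervention should be discontinued immediately and the reason for discontinuation should be recorded in a timely manner". Section 2.15.2 is similar: after an adverse reaction, participation ends and relevant information is recorded; a patient who asks to suspend is to stop the trial, with the reason noted. Both sections say that a patient's data are still recorded and counted if participation has lasted more than two weeks.

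Two statements point the other way. Section 2.13 says: "All patients will receive baseline assessment, 1-week post-intervention assessment and 2-week post-intervention assessment". Section 2.15.2 promises an intention-to-treat analysis "incorporating all randomly assigned participants, regardless of whether they withdrew prematurely".

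On the outcome itself, section 2.13 says only that "The primary outcome is the FMA-UE"; it names no primary time point.

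**The concern.** An assessment triggered by a session count exists for certain only for people who reach that session. A patient whose ES ends after session 7 has no tenth session, and the stopping text gives the site no other date for the week-2 FMA-UE. Section 2.15.2 also treats asking to suspend as leaving the trial, so stopping the needle treatment and ending outcome collection become one event. An analysis plan can choose a method for missing values, but it cannot recover a score that was never taken.

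If week-2 scores are lost because treatment stopped, the planned analysis drifts towards a comparison of completers. That is biased when stopping, or the prognosis of those who stop, differs by arm. A difference by arm is possible: current is raised to tolerance only in the trial group, the sham delivers none, and section 2.5 says that staff giving ES are not blind (section 2.4 says that they are).

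A patient who misses sessions raises a second question. The tenth session, and with it the week-2 score, falls later than for others, in people enrolled between two weeks and three months after onset, when natural recovery may still be under way.

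**Working it through.** **Reading the passages together, for a patient on schedule who stops after session 7**

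- Section 2.9: the week-1 assessment was done at session 5; the week-2 assessment belongs to a session that will not take place.
- Sections 2.12.4 and 2.15.2: stop and document. No later assessment is mentioned.
- The clause on more than two weeks does not help: the whole course is two weeks. Only someone whose sessions had already slipped could meet it before session ten.
- Section 2.13: this patient should nevertheless receive the 2-week assessment.
- Section 2.15.2: this patient is to be in the analysis.

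The first three leave the week-2 score unscheduled; the last two require or presuppose it.

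**The plan's own figure.** Section 2.2 inflates 20 per group "with a drop-out rate of around 20" per cent: 20 / (1 − 0.20) = 25 per group, which reproduces. The allowance is 25 − 20 = 5 per arm, or 10 of 50. This is an upper figure for missing week-2 scores by this route, since the allowance is not broken down and may include withdrawal of consent.

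**Bias of a completers' comparison.** Let p be the proportion stopping in an arm, and let the gap be the mean FMA-UE of completers minus that of stoppers, taken as equal in both arms. The full-arm mean is the completers' mean − p × gap, so the bias in the difference is (p active − p sham) × gap. Both pairs of assumed stop rates average the planned 20%.

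| Assumed stop rates, active v sham | Gap 3 points | Gap 5 points |
|---|---|---|
| 30% v 10% | 0.20 × 3 = 0.6 | 0.20 × 5 = 1.0 |
| 25% v 15% | 0.10 × 3 = 0.3 | 0.10 × 5 = 0.5 |

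Against the 5.25-point target, 0.3 / 5.25 = 6% and 1.0 / 5.25 = 19%.

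Equal stopping is no safeguard if stoppers differ from completers in one arm only. With 20% stopping and an assumed gap of 2 to 8 points in that arm, the shift is 0.20 × 2 = 0.4 to 0.20 × 8 = 1.6 points.

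**Delay.** With assumed natural recovery of 1 to 3 points a week, a tenth session 2 to 4 days late moves that patient's score by 1 × 2/7 = 0.3 to 3 × 4/7 = 1.7 points. This biases the group difference only if delays differ by arm; otherwise it adds noise.

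**Effect of the fix on power.** No SD is stated. Back-solving n = 20, a 5.25-point difference, two-sided 0.05 and 80% power with a t-test implies an SD of 5.77. On that SD, 25 assessed per group would give 88.3% power if stoppers showed the full effect. They may not: if 20% of the active arm gained nothing, the effect would be 0.80 × 5.25 = 4.2, below the roughly 5.25 × √(20/25) = 4.7 needed for 80% power with 25 per group. The case for the fix is therefore validity, not power.

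**The case against.** The strongest reply is that section 2.13 already requires the 2-week assessment for everyone, and that with five sessions a week the mention of session ten merely says where that visit falls on schedule. No passage forbids assessing a patient who has stopped. This stands in part: a reader might infer that an early stopper definitely has no final visit, but the documents support only that the visit has no clear date and that the passages conflict.

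Three other tempting readings also go too far:

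- That the intention-to-treat analysis would have no data for early stoppers. Each patient who completes the enrolment steps has a baseline FMA-UE, and anyone who reached session five should have a week-1 score.
- That only the reason is recorded after stopping. That holds for patient-initiated stopping; for intercurrent conditions and adverse reactions, the circumstances or relevant information are recorded too.
- That week 2 is the stated primary time point. It is the last assessment and a natural reading, but the article does not say so.

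It is also fair that an article condenses a fuller protocol, that Figure 2 is not shown, and that visit windows and missing-data methods are commonly set elsewhere. That disposes of any complaint about an absent window or imputation method. It does not dispose of the conflict between rules that the article does state.

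Finally, stopping that differs by arm is not established. Under sections 2.12.1 and 2.12.3, pain leads to a reduction in current and is not given as a reason to end ES. The stop rates, gaps and recovery rates used here are assumptions.

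**Conclusion.** The point holds as an inconsistency with a practical consequence. Followed as written, section 2.9 and the stopping text make it likely that patients who stop ES before session ten will lack a week-2 FMA-UE, while sections 2.13 and 2.15.2 presuppose one. Up to about 10 of 50 could be affected if the entire drop-out allowance arose this way. In the main illustration the bias is 0.3 to 1.0 point (6% to 19% of the 5.25-point target), resting on assumed stop rates of 25% v 15% to 30% v 10% and a gap of 3 to 5 points. With a gap in one arm only, of 2 to 8 points, it is 0.4 to 1.6 points. None of these inputs is in the document, and the bias could be nil if stoppers resembled completers.

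A reader might conclude that the intention-to-treat promise is empty. The documents do not support that, since earlier scores exist and could contribute. What they lack is a data-collection rule that matches the promise. In an exploratory two-week inpatient trial this is something to correct, not a fatal flaw.

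**What to change.** - In section 2.9 and Figure 2, define t2 and t4 by calendar day from randomisation (for example day 7 and day 14, each with a short window) for every randomised participant, whatever number of sessions was received. If the first session can follow randomisation by some days, choose the days so that they match the usual fifth and tenth sessions.
- In sections 2.12.4 and 2.15.2, separate stopping ES from withdrawing consent to assessment. Those who only stop ES keep the FMA-UE, EEG, NIHSS, MMSE and MBI assessments at t2 and t4; only withdrawal of consent to assessment ends collection. Record the number of sessions received.
- Reconcile sections 2.9, 2.12.4, 2.13 and 2.15.2, including the clause on more than two weeks. Section 2.6 must be brought into line as well: its list removes from analysis the data of patients who withdraw or comply poorly, so extra assessments would otherwise be collected and then discarded.

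None of this alters when ES is given or stopped.

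The cost is a few assessments in patients who have stopped ES, and an amendment needing ethics approval while recruitment is running (October 2024 to about September 2025). Participants are hospitalised and assessors are in place, so the added work is small. The estimate becomes the effect of being assigned to ES, somewhat diluted by patients with fewer than ten sessions, which is the quantity that an intention-to-treat analysis is meant to give. Scores of patients who withdraw consent would still be missing.
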